## Abstract

**Background:**

Incisional hernia is a frequent complication in abdominal surgery. This article describes the development of a prospective randomized clinical trial designed to determine whether watchful waiting is an acceptable alternative to surgical repair for patients with oligosymptomatic incisional hernia.

**Methods/Design:**

This clinical multicenter trial has been designed to compare watchful waiting and surgical repair for patients with oligosymptomatic incisional hernia. Participants are randomized to watchful waiting or surgery and followed up for two years. The primary efficacy endpoint is pain/discomfort during normal activities as a result of the hernia or hernia repair two years after enrolment, as measured by the hernia-specific Surgical Pain Scales (SPS). The target sample size of six hundred thirty-six patients was calculated to detect non-inferiority of the experimental intervention (watchful waiting) in the primary endpoint. Sixteen surgical centers will take part in the study and have submitted their declaration of commitment giving the estimated number of participating patients per year. A three-person data safety monitoring board will meet annually to monitor and supervise the trial.

**Discussion:**

To date, we could find no published data on the natural course of incisional hernias. To our knowledge, watchful waiting has never been compared to standard surgical repair as a treatment option for incisional hernias. A trial to compare the outcome of the two approaches in patients with oligosymptomatic incisional hernias is urgently needed to provide data that can facilitate the choice between treatment options. If watchful waiting was equal to surgical repair, the high costs of surgical repair could be saved. The design for such a trial is described here.

This multicenter trial will be funded by the German Research Foundation (DFG). The ethics committee of the Charité has approved the study protocol. Approval has been obtained from ten study sites at time of this submission. The electronic Case Report Forms have been created. The first patient was to be randomized November 14^th^, 2011. An initiation meeting took place in Berlin January 9^th^, 2012.

**Trial Registration:**

ClinicalTrials.gov: NCT01349400

## Background

Incisional hernias occur in 10-20% after elective abdominal incisions and are among the most frequent surgical complications after laparotomy [1]. Forty-four thousand incisional hernia repairs were performed in Germany in 2007 [2]. The treatment of incisional hernias thus represents a large surgical and socioeconomic problem.

A 2009 Danish study addressing the early postoperative outcome reported a major complication rate of 3.5%, an overall morbidity rate of 10.7%, and a mortality rate of 0.4%. The rehospitalization rate was 11.2% [3]. The long-term outcome of incisional hernia repair is even more unsatisfactory. Pain persists in 20% of the patients after hernia repair, and the recurrence rate after incisional hernia repair remains high despite the development of various tension-free techniques (10-50%) [4]. Since incisional hernia repair is not a low-risk operation, it should be performed only when definitely indicated.

Due to the risk of incarceration, surgery has thus far been regarded as the only reasonable therapy for patients with incisional hernia. An incarceration is defined as an acute retention of the hernia accompanied by acute severe pain. If not reduced or repaired immediately, the acute incarcerated hernia leads to impairment of perfusion of the hernal contents followed by necrosis. Acute incarceration is a serious complication associated with high mortality, which is significantly increased if resection of gangrenous bowel is required [5]. Other potential factors favoring surgical repair are enlargement of hernia with the consequence of more difficult repair and cosmetic reasons.

In fact, there have been no investigations concerning the actual risk of incarceration or risk factors for incarceration in the total population at risk. Some smaller studies have reported acute incarceration as the indication for surgery in 6.0 to 14.6% of incisional hernia repairs [6-9]. A pre-study in which we prospectively enrolled all patients with incisional hernia repair disclosed an emergency repair rate of 3.2% [10].

In a large prospective randomized trial, Fitzgibbons et al. demonstrated that the acute incarceration rate is low in inguinal hernias: 1.8 per 1000 patient-years in mildly symptomatic men [11]. The percentage of patients with pain and discomfort interfering with normal activities did not differ between watchful waiting and surgical repair after a 2-year follow-up [11]. Delaying surgical repair was found to have no adverse effect on subsequent surgery or the final outcome [12].

Besides medical considerations, health care cost containment is gaining increasing importance, and the cost-effectiveness of each procedure has to be taken into account. A comparison of tension-free repair and watchful waiting in men with minimally symptomatic inguinal hernias showed $1831 higher mean costs per patient for tension-free repair after a 2-year follow-up [13].

These randomized controlled trials indicate that watchful waiting should be considered in men with asymptomatic or minimally symptomatic inguinal hernia according to the European Hernia Society Guidelines, level of evidence 1B [14].

Many surgeons believe that repair of incisional hernias may become more difficult in the course of time due to hernia enlargement. Also, there is a lack of data on the natural course of incisional hernias (enlargement, pain and discomfort) and the subjective disturbance by the hernia for cosmetic reasons.

A relevant proportion of incisional hernia patients are already left without surgical correction, although there are virtually no data describing or predicting the natural course. Twenty-two percent of patients presenting with incisional hernia to outpatient departments of internationally renowned hernia surgeons received no surgical treatment. The percentage of patients submitted to surgical repair varied from 50 to 100% for different surgeons [15]. Obviously, the treatment of incisional hernias is not standardized even in experienced hands.

Due to evidence-based data, watchful waiting has become a reasonable option for minimally symptomatic inguinal hernias. The potential benefit of a watchful waiting strategy is the avoidance of a possibly unnecessary procedure with all its complications (e.g., wound infection, mesh infection, bowel injury, ileus, postoperative bleeding, recurrence, chronic postoperative pain) and cost containment. A randomized controlled trial comparing watchful waiting and surgical repair in oligosymptomatic incisional hernias is urgently needed to broaden our knowledge regarding the natural course of incisional hernias and to test watchful waiting as a treatment option.

## Methods/Design

### Objectives, endpoints and sample size calculation

This clinical trial is designed to investigate the hypothesis that watchful waiting is not inferior to surgical repair of asymptomatic and oligosymptomatic incisional hernias in terms of pain and discomfort during normal activities.

To rule out published or ongoing trials dealing with the same subject, a literature search was done. Searching PubMed using the terms "incisional hernia AND watchful waiting" retrieved no matching results. "Incisional hernia AND randomized trial" retrieved 180 hits, but no randomized trial comparing watchful waiting to surgical repair. By searching relevant websites http://www.clinicaltrials.gov, http://www.actr.org.au, http://www.umin.jp/ctr/index.htm, http://www.trialregister.nl, http://isrctn.org, no randomized trial comparing watchful waiting vs. surgical repair in incisional hernia could be identified.

The primary efficacy endpoint is pain/discomfort during normal activities as a result of the hernia or hernia repair 2 years after enrolment, as measured by the hernia-specific Surgical Pain Scales (SPS). Studies show that a long term follow up is needed because postoperative pain may decrease with time [16]. Participants are asked to rate the average pain during the last 24 hours on a 150 mm visual analog scale varying from "no pain sensation" to "most intense pain imaginable". The Surgical Pain Scales were introduced by McCarthy et al. Intraclass correlation coefficients for SPS were 0.95 and 0.94. Correlations varying from 0.44 to 0.60 between the visual analog scales and the bodily pain dimension on the SF-36 and significant differences between SPS levels for patients requiring more and less time to resume normal activities (p = 0.015 to p = 0.002) supported the validity of the scales [17]. SPS scores are measured at baseline and at follow-up visits after 6, 12, 18 and 24 months.

The sample size calculation is based on the non-inferiority of the experimental intervention. A mean SPS score of 12.0 with a SD of 12.0 and 12.0 and an expected mean difference of 0.5 in favor of the surgical intervention group is assumed after a two-year follow-up.

Thus, if both groups have a sample size of 286, a two-group 0.05 level one-sided t-test will have 80% power to reject the null hypothesis that watchful waiting is not equivalent to surgical repair in favor of the alternative that watchful waiting is not inferior to surgical intervention [18]. This leads to a total sample size of n = 2 × 286 = 572. Assuming a drop-out rate of about 10%, 636 patients will have to be allocated. Sample size calculation was done with nQuery 6.0.

The most important secondary endpoint (S1) is the cost of treatment. Hospitalization costs can be calculated yearly along the guidelines of the InEK (Institute for Hospital Reimbursement System) institute. Hospitalization costs in Germany are mapped by the German-Diagnosis Related Groups-System. Inpatient costs for each participant (operation; medical staff and nursing staff on ICU, on IMC and on general ward; medication; implants; bandaging and other material; catering; infrastructure; laboratory, radiological, endoscopic and cardiologic diagnostics) will be completely included. Hence, the exact costs of every patient can be calculated in Euro [19]. Indirect costs (time off from work) will be monitored by questionnaire during follow-up.

If the results show a statistical difference in the primary endpoint, S1 will also be tested for significance (hierarchical testing). We hypothesize lower costs in the watchful waiting group, and, if a statistical difference is found, patient satisfaction with care will be tested as another secondary endpoint S2. We also hypothesize superiority of the experimental intervention in the secondary endpoint S2 because surgery is avoided.

Additional secondary outcomes include pain at rest, pain during exercise, highest level of pain measured by the SPS [17]. The impairment of daily activities due to pain is measured by the German version of the Pain Disability Index (PDI). The German version of the PDI revealed objectivity, reliability (Cronbach's α 0.90) and factor and construct validity [20]. Principal axis factor analysis has been used to investigate the underlying dimensions of the PDI; parallel analysis and scree plot favored a single-factor solution [21]. The functional status and quality of life is measured by the 2^nd ^German version of the SF-36 questionnaire. The reliability of the German version of the SF-36 is satisfactory, the validity is adequate, and the correlation with another established quality of life questionnaire (Nottingham-Health-Profile) is high [22]. Depression/anxiety is assessed by the 3^rd ^German version of the Hospital Anxiety and Depression Scale (HADS-D). Sensitivity and specificity were both 0.80. Reliability is high (Cronbach's α 0.80) [23]. Postoperative complications (e.g., postoperative bleeding, hematoma/seroma, wound infection, mesh infection, intra-abdominal abscess, ileus, bowel obstruction, enterocutaneous fistula, bowel injury) and mortality are recorded.

The relative frequency of acute hernia incarceration (acute incarceration events/duration of hernia) is determined in the experimental group according to the Fitzgibbons' trial in inguinal hernia [24]. To document the natural course of the hernia and a potential enlargement, hernia size is measured by ultrasound in the watchful waiting group at enrolment and after a 2-year follow-up. Therefore, ultrasound of the abdominal wall is performed and the maximum diameter of the hernia is also determined. The recurrence rate is calculated in the control group.

A flow chart of the estimated number of screened patients and the number of randomized and analyzed patients according to the CONSORT 2010 statement for reporting parallel group randomized trials [25] is given in Figure 1.

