## Discussion

This article describes the design of a trial comparing surgical and nonsurgical management of incisional hernias. Incisional hernia repair is not a low-risk operation, and it is associated with a high recurrence rate and a high percentage of postoperative pain. Treatment of incisional hernias represents a large surgical and socioeconomic problem. Up to now, surgical treatment has been recommended for incisional hernia patients regardless of whether there are any symptoms indicating a high risk of acute incarceration with serious complications. No studies have as yet defined the exact indications for incisional hernia repair or described the natural course of an incisional hernia, including the risk of acute incarceration. Randomized controlled trials performed in the past few years have shown that watchful waiting is a reasonable option for mildly symptomatic inguinal hernias.

To our knowledge, this is the first study to compare watchful waiting with surgical repair of oligosymptomatic incisional hernias in a prospective randomized setting. The study will provide very useful information regarding the natural course of incisional hernias and the rate of incarceration. We hypothesize that pain intensity during everyday activities does not differ between the compared groups and that the incarceration rate is low. If this should be confirmed, it would be justifiable to apply a watchful waiting strategy for oligosymptomatic incisional hernias and to thus avoid the risks and costs of surgery.

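### The gate to the cost and satisfaction tests asks for a statistical difference in pain, although the primary hypothesis is non-inferiority; read literally, it stays almost always shut when the trial succeeds

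*Protocol article*

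**What the plan says.** All of the relevant design text is in the protocol article, under Objectives, endpoints and sample size calculation, except the last item.

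- The hypothesis is that "watchful waiting is not inferior to surgical repair of asymptomatic and oligosymptomatic incisional hernias in terms of pain and discomfort during normal activities".
- On sizing: "The sample size calculation is based on the non-inferiority of the experimental intervention". The test is described thus: "a two-group 0.05 level one-sided t-test will have 80% power to reject the null hypothesis", with rejection leading to the conclusion of non-inferiority.
- The gate to S1 (cost) reads: "If the results show a statistical difference in the primary endpoint, S1 will also be tested for significance (hierarchical testing".
- The gate from S1 to S2 follows a clause that hypothesises lower cost with watchful waiting: "if a statistical difference is found, patient satisfaction with care will be tested as another secondary endpoint S2".
- The Discussion states the expected primary result: "We hypothesize that pain intensity during everyday activities does not differ between the compared groups".

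Nowhere does the article restate the first gate in terms of non-inferiority being shown.

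**The concern.** In a fixed-sequence procedure, the next hypothesis is tested once the previous null has been rejected. Here that null is inferiority of watchful waiting by at least the margin, so the step to S1 should be taken when non-inferiority is concluded. The article instead names a statistical difference in pain. That is a separate result, and one the investigators say they do not expect.

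The confirmatory status of S1 and S2 is at stake. The abstract's rationale is that surgery's cost could be spared if waiting proves as good. Followed as written, the rule blocks the confirmatory cost test in that very situation. If the rule is instead reinterpreted once results are known, the cost claim can be challenged as resting on a hierarchy changed after the fact.

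**Working it through.** **Inputs.** The planning values are "A mean SPS score of 12.0 with a SD of 12.0 and 12.0 and an expected mean difference of 0.5 in favor of the surgical" arm. The test is one-sided at 0.05 with 80% power, and "This leads to a total sample size of n = 2 × 286 = 572". The margin is not printed in the article, so it is solved for below and treated as an assumption. The level and sidedness of the gate's difference are not given either, so two versions are shown.

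**Reproducing the plan's sample size.** SE = 12 × √(2/286) = 1.0035. The implied margin is 0.5 + 1.0035 × (1.645 + 0.842) = 2.995 by the normal approximation, or 2.998 by the non-central t. With a margin of 3.0, the exact t-test calculation returns 286 per group (power 80.05%). A margin of 2.5 would need 446 per group and a margin of 3.5 would need 199, so 3.0 is the value that fits. Drop-out: 572/0.9 = 635.6, rounded up to the stated 636.

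**Where each result falls.** Let D be the observed difference, waiting minus surgery, with positive values meaning more pain with waiting.

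- Non-inferiority is shown if D < 3.0 − 1.645 × 1.0035 = 1.35.
- A two-sided 5% difference needs |D| > 1.96 × 1.0035 = 1.97.
- Both can hold only if D < −1.97, that is, if waiting is significantly better.

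**At the planned true difference of 0.5 (normal approximation).**

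- P(non-inferiority) = Φ((1.349 − 0.5)/1.0035) = 80.1%.
- P(waiting significantly worse) = 1 − Φ((1.967 − 0.5)/1.0035) = 7.2%.
- P(waiting significantly better) = Φ((−1.967 − 0.5)/1.0035) = 0.7%.
- P(two-sided gate opens) = 7.2% + 0.7% = 7.9%.
- P(two-sided gate opens, given success) = 0.0070/0.8013 = 0.9%.
- Share of two-sided openings with waiting worse = 0.0719/0.0789 = 91%.

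**A one-sided 5% superiority gate** needs D < −1.645 × 1.0035 = −1.65. At 0.5 this has probability 1.6%, and given success 0.0161/0.8013 = 2.0%.

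| True difference | P(non-inferiority) | P(two-sided difference) | Two-sided gate open, given success | One-sided superiority gate open, given success |
|---|---|---|---|---|
| 0.5 (planned) | 80.1% | 7.9% | 0.9% | 2.0% |
| 0 | 91.1% | 5.0% | 2.7% | 5.5% |
| −0.5 (waiting better) | 96.7% | 7.9% | 7.4% | 13.0% |

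**Sensitivity to the assumed margin.** At a true difference of 0.5, the two-sided conditional figure is 1.1% for a margin of 2.5 and 0.8% for 3.5. The 7.9% and 91% figures do not involve the margin.

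**With the gate tied to non-inferiority**, it opens with the probability in the second column: about 80% at 0.5 and 91% at 0.

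**The case against.** The strongest reply is that the damage depends on a test the article never defines. The only primary test described is the one-sided non-inferiority test. When the article goes on to say that S1 is tested for significance as well, it is natural to refer back to that test and to take a significant primary result as rejection of its null. The wording nearby is loose in other ways too: the non-inferiority null is phrased as a lack of equivalence. On this reading the gate opens with about 80% probability and the fault is one of expression. This stands as a plausible account of intent. It does not rescue the sentence, because a difference and non-inferiority are distinct findings and this sentence is the article's only statement of the first gate. A statistical analysis plan that is not shown could supply detail, but the rule in the article would still be wrong as stated.

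Three further inferences a reader might draw are not supported:

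- **That the second gate is also broken**, because higher cost with waiting would open S2. The clause just before it hypothesises lower cost with watchful waiting, so the direction is already given. Repeating it in the gate is a clarification only.
- **That the gate opens mainly when waiting is worse.** This holds only if the gate is two-sided. A one-sided superiority gate never opens in that direction, though it too is mostly shut.
- **That S1 and S2 must use the primary test's one-sided level.** The article does not say this and the defect does not require it.

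**Conclusion.** The first gate is wrong as written. It names a statistical difference where the design calls for non-inferiority shown. Read literally, it opens in about 0.9% of successful trials at the planned difference of 0.5 and 2.7% at no difference (two-sided 5%), or about 2.0% and 5.5% (one-sided 5% superiority). These figures rest on a margin of 3.0 inferred from the stated sample size and on an assumed level and sidedness for the gate. Varying the margin from 2.5 to 3.5, or the sidedness, does not change the conclusion.

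A reader might infer that the trial will in practice fail to test cost. The documents do not establish that, because the authors may have intended the non-inferiority null. Nor do they support a wider claim against the trial: the primary hypothesis, the primary test and the sample size are untouched. Under Table 1, costs and satisfaction are collected whatever the primary result, and can be reported descriptively. The point concerns the confirmatory standing of two secondary endpoints.

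**What to change.** Replace the gating sentence with: *If non-inferiority of watchful waiting is shown in the primary endpoint, S1 will be tested for lower cost with watchful waiting; if S1 is significant in that direction, S2 will be tested for superiority of watchful waiting.*

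The level and sidedness of the S1 and S2 tests can be left to the statistical analysis plan. The cost is one sentence, with no change to patients, sample size, data collection or the primary analysis. It should be made and dated before outcome data are analysed, so that the hierarchy cannot be said to have been chosen after the result.

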**Figure 1 F1:**
[figure not shown]
**Estimated trial flow of the study**.

### Inclusion and exclusion criteria

Inclusion and exclusion criteria were chosen broadly to provide generabilizability. Patients are eligible for enrolment if they meet both of the following criteria: 1) age ≥ 18 years, 2) asymptomatic/oligosymptomatic incisional hernia (patients with recurrent incisional hernias are eligible).

Patients are excluded if they meet any one of the following criteria: 1) no hernia detectable on physical examination, 2) acute incarcerated hernia, 3) emergency hernia repair, 4) hernia-related pain or discomfort during normal activities, 5) local or systemic infection, 6) ASA score > 3, 7) inability to complete or comprehend the preoperative questionnaire, 8) repair with biologic prosthesis.

### Implementation of the study

All patients presenting to the outpatient clinic with a possible incisional hernia are screened for trial eligibility. Those who have no unequivocal contraindications are scheduled to see the participating surgeon to confirm that they are candidates for the study. Informed consent is obtained for participation and randomization after taking a thorough history, performing a physical examination and checking for inclusion and exclusion criteria. Randomization will be done by an electronic randomization tool created by the Coordinating Center for Clinical Studies (KKS Charité). After obtaining the patient's informed consent, the site coordinator will log into the password-protected electronic randomization tool, which provides stepwise explanations. Randomization will be stratified by study center, hernia size (< 4 cm vs. ≥ 4 cm) and planned surgical repair (laparoscopic vs. open).

In primary analysis, adjustment for strata will be performed. We will additionally perform subgroup analyses within the strata and present the individual 95%-CIs. Furthermore, strata specific effect size calculations are planned if necessary.

Considering the lack of a prospective study on incisional hernia repair and the variety of repair techniques, many different methods can be adopted to enable generalizability and adequate recruitment.

Open incisional hernia repair will be performed with mesh (non-absorbable or partly absorbable alloplastic material) or sutures. Laparoscopic repair will be performed with non-absorbable or partly absorbable mesh in intraperitoneal onlay position (IPOM). The surgeon performing the operation can choose the optimal approach. Sublay mesh repair with closure of the peritoneum is recommended for hernias measuring ≥ 3 cm. IPOM, inlay or onlay repair are also permitted. The mesh should widely overlap the fascial margin (≥ 4 cm) on all sides. In non-mesh repair, either direct suture repair or the Mayo procedure [26] can be performed. The type of repair, the type of mesh, the suture material, the suturing method, and the peritoneal and fascial closure have to be documented to identify potential differences by subgroup analysis.

Participants randomized into the watchful waiting group will receive standardized oral information and written instructions which, like those described by Fitzgibbons et al., will deal with physical activity, diet, pain and pain medication, constipation management, sexual activity, hernia warning signs, and symptoms of acute incarceration [24]. They will be told to consult a physician immediately if acute symptoms develop. Physical examinations will be performed during follow-up visits at 1 month, 12 months and 24 months by a physician. After 6 and 18 months, participants will also be interviewed regarding potential hernia-related pain or discomfort by a physician or a study nurse. The frequency and scope of study visits is presented in table 1.

**Table 1 T1:** Frequency and scope of study visits

Visit	Visit 1 (Screening)	Visit 2 (Day of surgery)	Visit 3 (1 month post OP)	Visit 4 (6 months post OP)	Visit 5 (12 months post OP)	Visit 6 (18 months post OP)	Visit 7 (24 months post OP)
Demographics and baseline clinical data	X						

Inclusion/exclusion criteria	X						

Randomization	X						

Clinical examination	X		X		X		X

Ultrasound	X						X

Pain level (SPS, PDI)	X			X	X	X	X

Quality of life (SF-36)	X			X	X	X	X

Mental health (HADS-D)	X						X

Patient satisfaction (Likert scale)	X			X	X	X	X

Surgical intervention		X					

Postoperative complications			X		X		X

AEs/SAEs		X	X	X	X	X	X

Costs of treatment		X	X	X	X	X	X

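### Baseline SPS is collected but not named in the stated adjustment of the primary analysis; adding it is a cheap improvement with a probably small gain in power

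*Protocol article*

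**What the plan says.** Under *Implementation of the study*, the protocol article describes randomisation stratified by centre, hernia size (cut at 4 cm) and planned surgical approach, and then says: "In primary analysis, adjustment for strata will be performed". It names no model and no further covariate.

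Under *Objectives, endpoints and sample size calculation*, the primary endpoint is the SPS score for pain during normal activities two years after enrolment, and "SPS scores are measured at baseline and at follow-up visits after 6, 12, 18 and 24 months". Table 1 shows the same measurement plan. The sample size rests on "A mean SPS score of 12.0 with a SD of 12.0 and 12.0", on "an expected mean difference of 0.5 in favor of the surgical intervention group", and on the statement that "a two-group 0.05 level one-sided t-test will have 80% power". The total follows: "This leads to a total sample size of n = 2 × 286 = 572", and then "Assuming a drop-out rate of about 10%, 636 patients will have to be allocated".

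Under *Monitoring and statistical analysis*, the primary analysis follows the intention-to-treat principle, with additional as-treated analyses. The article does not describe how missing 24-month scores are handled.

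**The concern.** The baseline value of a continuous outcome is often its best available predictor. Conditioning on it removes chance imbalance between the arms and any outcome variance that it explains. Here the article commits itself to an adjustment set for the primary analysis, and that set consists of three design factors without baseline SPS, which is already on the visit schedule.

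Precision matters in this trial. The planned standard error of the difference is about 1.0 SPS unit, and the distance from the expected difference to the implied margin is about 2.5 units. Power is planned at 80%, with no reserve. If baseline SPS carries information about the 24-month score, leaving it out gives up power that costs nothing to obtain.

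**Working it through.** **Inputs.** From the article: SD 12.0 in both arms, expected difference 0.5 in favour of surgery, one-sided 5% t-test, 80% power, 286 per arm, about 10% drop-out. Not in the article, and therefore assumed: the non-inferiority margin, the correlation ρ of baseline with 24-month SPS, and the correlation between follow-up visits.

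**1. The plan's own figure.** The stated inputs alone do not give 286, because no margin is stated. Solving for it:

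- standard error = 12 × √(2/286) = 1.0035
- margin = 0.5 + 1.0035 × (1.645 + 0.842) = 2.995, so about 3.0

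With a margin of exactly 3.0, the normal approximation needs 285 per arm and the t-test needs 286, with power 80.05%. The drop-out step reproduces directly: 572 / 0.9 = 635.6, rounded up to 636. Everything below uses a margin of 3.0, so the distance to be detected is 3.0 − 0.5 = 2.5.

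**2. Adding baseline SPS.** With a linear baseline covariate, the residual SD is 12 × √(1 − ρ²). The non-centrality is 2.5 / (residual SD × √(2/286)). Power comes from the non-central t distribution with 570 degrees of freedom; the one degree of freedom used by the covariate is immaterial here.

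| Assumed ρ | Residual SD | Non-centrality | Power at 286 per arm | n per arm for 80% (normal approximation) |
|---|---|---|---|---|
| 0 | 12.00 | 2.491 | 80.1% | 285 |
| 0.1 | 11.94 | 2.504 | 80.4% | 283 |
| 0.2 | 11.76 | 2.543 | 81.5% | 274 |
| 0.3 | 11.45 | 2.612 | 83.2% | 260 |
| 0.4 | 11.00 | 2.718 | 85.8% | 240 |
| 0.5 | 10.39 | 2.877 | 89.0% | 214 |

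**3. Which part of the range is plausible.** Exclusion criterion 4 (*Inclusion and exclusion criteria*) keeps out patients with hernia-related pain in the very domain that the primary endpoint measures. Baseline scores on that item should therefore have little spread, which points to a low ρ. For ρ up to 0.3 the gain is about 0 to 3 percentage points.

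**4. What the intermediate scores would add.** Take 318 randomised per arm, 10% drop-out spread evenly over the four follow-up visits, equal correlation between visits, missingness at random and no baseline covariate. The large-sample power of a repeated-measures likelihood model for the 24-month contrast is then:

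- 24-month scores alone: 80.2%, from 318 × 0.9 ≈ 286 per arm
- between-visit correlation 0.3: 80.5%, effective n 289
- correlation 0.5: 81.0%, effective n 294
- correlation 0.7: 81.7%, effective n 299

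The gain is about 0.4 to 1.5 points. It is small because these scores inform the 24-month mean only through the 10% who leave. With baseline SPS at ρ = 0.2 in the same model, power is 81.9% to 83.0%.

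**The case against.** The strongest reply is that this is a condensed article. Its sentence on strata does not say that nothing else is adjusted for, and the full protocol or the SAP may already contain baseline SPS. Adjusting for stratification factors is sound practice. The t-test is a sizing device, and sizing on an unadjusted test before analysing with adjustment is normally conservative, so no shortfall in power is shown. With exclusion criterion 4 in force, the gain may be negligible.

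Most of this stands, and it limits the point to a modest improvement. What it leaves untouched is that the article does state the adjustment for its primary analysis, that the outcome's own baseline is not in it, and that adding it cannot materially reduce power at 286 per arm.

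A reader might go further and infer that the analysis is restricted to completers, that patients who drop out contribute nothing, and that the false non-inferiority rate is therefore inflated. The documents do not support this. The step from 572 to 636 is a routine allowance in a sample size; it defines neither an analysis set nor a missing-data method. The only stated principle is intention to treat, and missing-data handling is commonly left to documents not shown. Any figure for false non-inferiority would need the unstated margin, an invented pain excess among watchful-waiting drop-outs, and no comparable excess among surgical drop-outs. The article's own *Background* reports persistent pain in 20% after repair, so the last condition cannot be taken for granted.

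**Conclusion.** The point holds as a recommendation to add one covariate. The article names the strata and not baseline SPS, and baseline SPS is collected. The likely gain is about 0 to 3 points of power (correlation up to 0.3), and about 9 points if the correlation were 0.5. These figures rest on a margin of 3.0 that is back-solved and not stated, and on correlations that the documents do not give.

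Using the 6-, 12- and 18-month scores is optional. Their value lies in letting patients who leave early contribute under missingness at random; they bring little power, and they do not protect against drop-out that depends on unobserved pain.

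**What to change.** State that the primary comparison of 24-month SPS is adjusted for the stratification factors and for baseline SPS as a prespecified covariate. If the SAP already says so, confirming it closes the point.

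Optionally, analyse SPS at 6, 12, 18 and 24 months as repeated outcomes in all randomised patients, with the 24-month contrast as the primary estimate. The intermediate scores are post-randomisation values, so they may enter as outcomes or in imputation but not as covariates. Visit timing must be aligned first: the endpoint definition counts from enrolment, whereas Table 1 counts follow-up from the operation, which does not fit the watchful-waiting arm. A sensitivity analysis for data not missing at random would still be needed.

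The covariate costs one degree of freedom and a sentence of wording, fixed before treatment codes are released. No extra data are needed. The repeated-measures option costs a more complex model and the timing clarification.
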